#### Secondary outcomes

The parents’ health-related quality of life will be assessed by the German version of the EuroQoL-5 (EQ-5D) [22–24]. The quality of life in parents will be assessed by the Ulm Quality of Life Inventory for Parents (ULQIE) [25]. In addition, quality of life in parents will be assessed with the 12-Item Short Form Health Survey (SF-12) [26]. The health-related quality of life of the diseased children will be assessed by the DISABKIDS Chronic Generic Measure-37 (DCGM-37) [27]. The health-related quality of life of both diseased children and their siblings will be assessed by the KIDSCREEN-27 [28]. A short version of the KIDSCREEN-27, the KIDSCREEN-10, will be used for the calculation of quality-adjusted life years for children and adolescents [29, 30].

The parent’s symptomatology will be assessed by the German version of the Brief Symptom Inventory (BSI) [31], a short version of the Symptom Checklist-90-Revised (SCL-90-R). In addition, the German version of the Patient Health Questionnaire (PHQ-D) [32] will be applied to screen for depressive, anxiety, somatoform, alcohol, and eating disorders. Further aspects of the parental psychopathology will be assessed by the German version of the Global Assessment of Functioning (GAF) [33], which is used to rate a person’s overall level of functioning.

The children’s psychopathology will be assessed using the German version of the Kiddie Schedule for Affective Disorders and Schizophrenia Present and Lifetime Version (K-SADS-PL) [34]. The K-SADS-PL is a standardized semi-structured interview for an early diagnosis of mental disorders in children and adolescents according to ICD-10 and DSM-IV criteria. Interviews on the children’s psychopathology will be conducted about each child using the parent-proxy version as well as the self-report version for children 10 years or older. In addition, the children’s global level of functioning will be assessed by the German version of the Children Global Assessment Scale (CGAS) [35].

Children’s psychopathology will further be assessed by the German version of the Child Behavior Checklist (CBCL) [36] and the Youth Self Report (YSR) [37]. Both questionnaires describe a variety of internalizing and externalizing behaviors in children.

Coping of the parents will be assessed with the Coping Health Inventory for Parents [38] and coping strategies of the children will be assessed with the KidCOPE [39].

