#### Data assessment and data management

The study design is illustrated in Fig. 1. At the beginning of the study, after signing the informed consent forms, the parents caring for a child with rare diseases will fill in the baseline questionnaires and participate in the structured clinical interviews, SCID-I about themselves and K-SADS-PL about their child/children. All children aged 10 years and older will also be asked to complete this diagnostic process if possible. As soon as all documents are complete, the family will be randomized into one of four groups. The research staff will subsequently inform the family about their group assignment and provide feedback on the results of the diagnostic interviews.

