The primary outcome, parent’s psychopathology measured by the SCID-I, is evaluated according to the intention-treat (ITT) principle. The ITT population consists of all randomized families for which baseline documentation is available. As the members of a family live under common conditions and interact with each other, cluster effects can be assumed. Thus, the inferential statistics are performed with mixed models. The primary outcome is binary (diagnosis according to SCID-I yes/no). A mixed logistic regression with family and family member as random effects, recruitment center, therapy group (2 factors: 1st factor CARE-FAM yes/no, 2nd factor WEP-CARE yes/no), and time as fixed effects within the ITT population of all initially conspicuous parents is performed. The interactions between time and the therapy groups is determined. If they are not significant, they are eliminated from the model. Missing values are treated by direct imputation to allow an ITT analysis. Under the assumption of two stochastically independent interventions, the contrast of each group factor at T4 is tested at the 5% level (two-sided hypothesis). Thereby, each intervention can prove to be effective on its own. Only these results are interpreted in a confirmatory manner. In an additional analysis, we test the assumption of independence by examining the interaction between both therapy group factors. The primary analysis is repeated in the per protocol population, which consists of all families with at least three sessions in CARE-FAM or WEP-CARE. To assess the effect of the interventions within specific subgroups, the following subgroup analyses are performed regarding study center, disease of children, age of the children, and disease of parents. In a series of sensitivity analyses, missing values are imputed by different approaches as last observation carried forward, multiple imputation, worst- and best-case imputations. Secondary outcomes are investigated exploratively without adjustment for multiplicity in the ITT population. The analysis strategy for the secondary, binary outcomes is the same as in the primary analysis. For secondary, continuous outcomes, linear mixed models with differences to baseline as outcome, family and family member as random effects and the same fixed effects as in the above-mentioned model and respective baseline value as covariate are examined. The safety outcomes are determined using frequency tables and if possible, with mixed logistic regression analogue to the primary analysis. Odds ratios or adjusted means, their 95% confidence interval, and *p* values are reported according to the CONSORT statement. Interim analyses are not planned. Statistical analyses will be carried out with standard statistical software.

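### Binary secondary outcomes inherit a primary model without a baseline term, although in the ITT population baseline status varies and continuous secondary outcomes are adjusted for it

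*Protocol article*

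**What the plan says.** All the relevant rules stand in the Data analysis section of the protocol article.

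- Primary model: "A mixed logistic regression with family and family member as random effects, recruitment center, therapy group (2 factors" are CARE-FAM yes/no and WEP-CARE yes/no), "and time as fixed effects within the ITT population of all initially conspicuous parents is performed". No baseline term is listed.
- Population for secondary outcomes: "Secondary outcomes are investigated exploratively without adjustment for multiplicity in the ITT population". That population is defined without regard to baseline diagnosis: "The ITT population consists of all randomized families for which baseline documentation is available".
- Binary secondary outcomes: "The analysis strategy for the secondary, binary outcomes is the same as in the primary analysis".
- Continuous secondary outcomes are modelled as differences to baseline, with "the same fixed effects as in the above-mentioned model and respective baseline value as covariate are examined".

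Baseline values exist. Before randomization the parents "participate in the structured clinical interviews, SCID-I about themselves and K-SADS-PL about their child/children", and Table 2 schedules the K-SADS-PL at baseline, 6, 12 and 18 months with an external rater. The Secondary outcomes section describes it as a diagnostic tool: "The K-SADS-PL is a standardized semi-structured interview for an early diagnosis of mental disorders in children and adolescents".

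**The concern.** The primary model can omit the baseline diagnosis because everyone analysed has one. That reason disappears when the same model is used in all randomized families: some children will have a diagnosis at baseline and others will not, and the same holds for a PHQ-D screening status in parents. The baseline status is measured before randomization in every arm and is likely to predict the later status. Followed as written, the rule ignores it for binary outcomes, while the neighbouring rule uses it for continuous ones.

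At stake is the power of the exploratory comparisons on diagnoses, in particular those of children, whose mental health is named under Study objectives. Two measures of the same domain, one scored and one diagnostic, would also be adjusted differently for no stated reason.

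**Working it through.** **1. The rules side by side**

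| | Primary | Binary secondary | Continuous secondary |
|---|---|---|---|
| Population | Initially conspicuous parents in the ITT population | ITT population | ITT population |
| Baseline status | Constant | Varies | Varies |
| Baseline covariate | None, none needed | None listed | Listed |

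Only the middle column has a varying baseline and no term for it.

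**2. The plan's own figure**

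The Sample size section needs 296 initially conspicuous parents, so 148 per level of each factor, for 91.2% against 80% non-conspicuous at 80% power and two-sided 5%.

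- Unpooled formula: n = (1.960 + 0.842)² × (0.912 × 0.088 + 0.80 × 0.20) / 0.112² = 7.851 × 0.2403 / 0.01254 ≈ 150.4, so 151 per level.
- Power at 148: SE = √(0.2403/148) = 0.0403, z = 0.112/0.0403 = 2.78, power = Φ(2.78 − 1.96) = 79.4%. Exact binomial enumeration gives 79.98%.

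The figure reproduces, and the present point does not change it. It also supplies the only persistence rate in the document: 80% non-conspicuous without CARE-FAM means that 20% of initially conspicuous parents remain so at 18 months.

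**3. Illustration of what adjustment gains**

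Assumed, because the article gives none of these for children: 600 children, 300 per level of one factor; 30% with a baseline diagnosis (the rate the article assumes for parents); 5% new diagnoses among the rest; odds ratio (OR) 0.50 given baseline status; one follow-up visit; no clustering. Persistence in the comparison group is varied.

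*Without baseline:* the overall risk in each arm is 0.30 × persistence + 0.70 × incidence. The SE of the log OR is √(1/[300·p(1−p)] + 1/[300·p′(1−p′)]), with p and p′ the two overall risks.

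*With baseline:* each baseline stratum has weight w = 1/(1/[n·p(1−p)] + 1/[n·p′(1−p′)]), with n = 90 per arm (diagnosis) or 210 (none), and SE = 1/√Σw.

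Power in both cases is Φ(|log OR|/SE − 1.96).

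Worked at 50% persistence:

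- Halving the odds turns 50% into 33.3% and 5% into 2.56%.
- Overall risks are 0.30 × 0.50 + 0.70 × 0.05 = 18.5% and 0.30 × 0.333 + 0.70 × 0.0256 = 11.8%. The unadjusted OR is 0.589, SE 0.233, z = 2.27, power 62.3%.
- Adjusted weights are 1/(1/22.5 + 1/20) = 10.59 and 1/(1/9.975 + 1/5.247) = 3.44. Then SE = 1/√14.03 = 0.267, z = 0.693/0.267 = 2.60, power 73.8%.

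| Persistence | Unadjusted OR (SE) | Power | Adjusted OR (SE) | Power | Gain, points |
|---|---|---|---|---|---|
| 20% | 0.515 (0.328) | 52.6% | 0.50 (0.335) | 54.5% | about 2 |
| 50% | 0.589 (0.233) | 62.3% | 0.50 (0.267) | 73.8% | about 11 |
| 70% | 0.674 (0.202) | 49.8% | 0.50 (0.270) | 72.7% | about 23 |

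The adjusted SE is larger, but the conditional log OR grows by more, so power rises. The unadjusted OR nearer 1 is not a biased estimate. It is the population-average quantity, which differs from the conditional one because odds ratios are not collapsible.

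**4. A second set of assumptions**

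A simulation used 620 × 0.8 = 496 children, one per family, 30% prevalence, and effects set to give about 77% unadjusted power. Unadjusted against adjusted power was 77% and 81% at a baseline-to-follow-up correlation (phi) of 0.3, 77% and 88% at 0.5, and 76% and 92% at 0.6. Direction and order of size agree.

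**The case against.** **The restriction may carry over.** The primary strategy includes a restriction to the initially conspicuous, so using the same strategy could mean analysing initially conspicuous children only. Baseline status would then be constant and the point would fall away. This reading is possible but less literal: the restriction is worded for parents, and the secondary outcomes are assigned to the ITT population. It stands as a reason to let the authors choose.

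**Time may include baseline as a response.** This is unlikely. In the primary set the baseline outcome is the same for everyone, so such a row would carry no information. If only follow-up visits enter, the family-member random effect does not use the baseline value.

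**No binary secondary endpoint is named.** Correct. That the K-SADS-PL is analysed as yes/no is inferred from its being a diagnostic interview; the same goes for the PHQ-D as a screener. The CBCL, YSR and CGAS, if analysed as scores, already get baseline adjustment.

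**Covariates can wait for the analysis plan.** For an unstated detail, yes. Here the article states a rule which, as written, leaves the baseline value out.

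**A reader might infer bias.** It is tempting to say that a chance imbalance in baseline diagnoses distorts the result. The documents do not support that as a charge of bias. Under randomization the unadjusted test is valid, and chance imbalance is already part of its standard error. Nor does the article set a power target for any child outcome that could be missed.

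**Conclusion.** The point holds as a loss of power and an inconsistency between two adjacent rules. It is not a validity problem. It concerns exploratory outcomes only; the two confirmatory contrasts and the sample size are untouched.

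The size cannot be fixed from the document. About 2 points of power are at stake if child diagnoses persist at the 20% assumed for parents without CARE-FAM, and about 23 points at 70%. A reader might take the upper end as the expected loss, but nothing in the article says how stable child diagnoses are. The calculations rest on assumed prevalence, incidence, effect and number of children, use a single visit and ignore family clustering, so they show a range and do not evaluate the planned mixed model.

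The change is worth making because it is nearly free and follows the plan's own continuous-outcome rule.

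**What to change.** In the Data analysis section, replace the sentence on binary secondary outcomes with wording such as: *Secondary binary outcomes are analysed in the ITT population with the mixed logistic model of the primary analysis, with the follow-up visits as response and the respective baseline status (for example K-SADS-PL diagnosis yes/no) as an additional fixed-effect covariate.*

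If the intention was to analyse only children who were conspicuous at baseline, state that restriction instead. No baseline term is then needed.

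The cost is one sentence and one model term, with no new data. There are two small downsides: the odds ratio becomes conditional on baseline status and should be reported as such, and family members without a baseline value must be covered by the missing-data rule or they drop out of this model.

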
## Discussion

This study presents an opportunity to implement two family-based intervention programs for families caring for children with rare diseases in German standard care. In the current trial, the program’s effectiveness and cost-effectiveness will be evaluated in a randomized-controlled design with a comprehensive health-economic assessment at baseline, 6, 12, and 18 months.

An important strength of this study is the use of a randomized controlled trial design with a combination of both interventions (CARE-FAM + WEP-CARE) and a control group receiving TAU, meaning no intervention within this study. This will be a stronger test of the intervention’s effectiveness. Moreover, the study design will include a comprehensive health-economic evaluation. The broad nature of the inclusion criteria will enable families of patients with a variety of rare diseases to take part in the study.

A wide range of psychosocial outcomes for both children and parents (e.g., mental health, health-related quality of life, coping, social support, family relationships) will be assessed. The outcomes concerning the children will not only be measured from the parents’ perspective; self-ratings of the children will also be obtained for all children aged 10 years and older. Most importantly, the parents’ and children’s mental health will be assessed by an external rater blind to the family’s assigned group.

This extensive assessment of outcomes will allow for a comprehensive analysis of various factors influencing the interplay of the mental health between the parents and their children.

An important implication for practice is that all family members participating in the study will be screened for mental health problems at the very beginning of study participation. This will provide an opportunity for early detection of mental illness, for which appropriate offers of assistance can subsequently be recommended.

Difficulties could arise from the multicenter design of this study. The combination of both university and supply clinics could lead to differences in the recruitment process. Hence, possible center effects will be statistically taken into account.

Moreover, the standardised execution of the manualised face-to-face intervention might prove difficult. A great number of therapists from different therapeutic approaches will conduct the CARE-FAM program. To ensure the implementation according to the manuals, the process and the methods of each sessions and the writing tasks will be documented and later analysed for compliance with the manuals.

Experience from this trial will be used to revise the existing manual. The financing of the intervention in regular care beyond the term of the study will be discussed with health-insurance representatives during the term. As a result, we aim to not only evaluate the CARE-FAM and WEP-CARE intervention in the participating study centers, but to also implement it into regular care throughout Germany.

The support provided to families caring for children with rare diseases should be comprehensive and integrative and therefore be oriented towards all family members, as the psychosocial and medical care for the affected families is equally complex. If successful, both interventions could be the first programs for affected families to be implemented into regular practice nationwide in Germany; this could be an important, future-oriented contribution to the improvement of a family-oriented support system for this particularly burdened group.

## Data Availability

The datasets generated during the current study will be made available in the repository of ClinicalTrials.gov (NCT04339465) once the data entry is complete.

## Abbreviations

BSI: Brief Symptom Inventory
CAMHSRI: Children and adolescent mental health services receipt inventory
CARE-FAM: Children Affected by Rare Disease and their Families
CBCL: Child Behaviour Checklist
ChEDE-Q8: Eating Disorder Examination Questionnaire for Children
CSSRI-DE: Client Socioeconomic and Services Receipt Inventory
DCGM-37: DISABKIDS Chronic Generic Measure-37
DSM-IV: Diagnostic and Statistical Manual for Mental Disorders, 4th Edition
EDY-Q: Eating Disorders in Youth-Questionnaire
EQ-5D: EuroQoL-5
FB-A: Allgemeiner Familienfragebogen
FBB: Fragebogen zur Beurteilung der Behandlung
FKV: Freiburger Fragebogen zur Krankheitsbewältigung
GAF: Global Assessment of Functioning
GARF: Global Assessment of Relational Functioning Scale
K-SADS-PL: Schedule for Affective Disorders and Schizophrenia for School Aged Children
OSSS: Oslo Social Support Scale
PHQ-D: Patient Health Questionnaire
SCID-I: Structured Clinical Interview for DSM-IV
SF-12: 12-Item Short Form Health Survey
SRQ: Sibling Relationship Questionnaire
TAU: Treatment as usual
ULQIE: Ulm Quality of Life Inventory for Parents
VPPS: Vanderbilt Psychotherapy Process Scales
WEP-CARE: Web-Based Psychological Support Program for Caregivers
YSR: Youth Self Report
ZUF-8: Fragebogen zur Messung der Patientenzufriedenheit
